## Abstract

**Background:**

Meaning-Centered Psychotherapy (MCP) is effective in improving meaning in life, hope, optimism, self-efficacy, well-being, and quality of life, and in reducing stress in people with cancer. However, all the studies on the application of MCP in cancer patients have been carried out in Anglo-Saxon samples. Therefore, it is necessary to adapt and verify the efficacy of MCP in populations that speak languages other than English, such as Spanish. Moreover, to expand the data supporting the efficacy of MCP for cancer patients, it would be necessary to compare MCP to other active therapies such as Cognitive Behavioral Therapy (CBT).

**Methods:**

The aims of the proposed study are: the first objective is to verify the efficacy of the MCP intervention for Spanish participants with cancer in a randomized control trial (RCT) comparing it to CBT. The second objective is to analyze the feasibility and acceptance of MCP in Spanish participants with cancer. The third objective is to analyze whether the changes produced in the meaning in life dimensions (presence, search, comprehension, purpose, and mattering) will predict changes in anxiety, depression, quality of life, etc. Our research team adapted MCP for Spanish participants with cancer. This paper presents the study protocol. The study design consists of a two-arm RCT with two conditions: MCP and CBT, where participants will be randomized to one of the two groups. Eligible participants will be adults with stage I, II, and III cancer who were treated with curative intent and had completed their main medical treatment (surgery, radiotherapy, or chemotherapy). Participants will be assessed at pretreatment, post-treatment, and 6-month follow-up. The intention-to-treat principle will be used when analyzing data, using mixed-effects models with full information and maximum likelihood estimation.

**Discussion:**

This study will provide results that confirm the efficacy of the MCP in Spanish participants with cancer.

**Trial Registration:**

ClinicalTrials.gov; https://register.clinicaltrials.gov/prs/app/template/Home.vm?uid=U0005WS9&ts=4&sid=S000BOTT&cx=bvr2ue, identifier NCT05197348

## Introduction

Being diagnosed with and coping with cancer is one of the most difficult and challenging life experiences a person can have. People with cancer have twice as much psychopathological distress as the cancer-free population, and the levels of depression in survivors in the first year after treatment are very high compared to the general population (1). In addition, anxiety, fatigue, sadness, emotional, and physical pain, poor quality of life, hopelessness, desire for hastened death, and low meaning in life are common negative emotional states in people with cancer and survivors (2–4).

Studies in clinical and non-clinical samples of patients without a cancer diagnosis have shown that meaning in life is an emotional state that is negatively associated with hopelessness, anxiety, emotional dysregulation, coping capacity, and depression, and it is a buffer against psychopathology (5, 6). Specifically in people with cancer, previous studies have found that meaning in life could buffer against depression, hopelessness, and the desire for hastened death (7). Therefore, previous studies suggest that intervening in meaning in life in cancer patients can be an effective treatment to improve the aforementioned negative emotional states and lead to better coping with life after a cancer diagnosis (8, 9).

Meaning-Centered Psychotherapy (MCP) is a logotherapeutic-oriented psychotherapy based on Viktor Frankl's (10, 11) principles and premises, such as the will to meaning, meaning in life, responsibility, freedom, finding meaning through courage and commitment, living one's legacy, and finding a sense of meaning through the three sources of meaning: creative, experiential, and attitudinal sources. MCP has been utilized in several samples and settings, and a meta-analytic study found that MCP is effective in improving meaning in life, hope, optimism, self-efficacy, wellbeing, and quality of life, and in reducing stress (12).

The MCP application for cancer patients was initially developed by Breibart as an eight-session group therapy for patients with advanced stage III-IV cancer (8). In a randomized control trial (RCT), it was shown to be more effective than supportive psychotherapy in improving spiritual wellbeing, sense of meaning, and anxiety, and the treatment effects of MCP were stronger 2 months after treatment. However, there were no significant differences in the participants' depression. Subsequently, Breibart (13), in an RCT with patients with stage III or IV cancer, adapted the MCP to seven sessions to be applied individually. Individual MCP was compared with a control group (massage therapists), and the results showed that MCP produced a greater improvement in meaning in life, spiritual wellbeing, faith, physical symptoms of distress, burnout, and quality of life. However, the improvement was not sustained at 2 months. The same authors indicated that there were no statistically significant improvements in depression or anxiety. The authors suggested that MCP may be more effective in a group format than in an individual format. MCP was later adapted by Rosenfeld (14) for palliative care (MCP-Palliative Care) by reorganizing the contents of the original MCP to reduce it to only three sessions. A pilot study was conducted on the feasibility, acceptability, and perceived utility of MCP in 12 patients with life expectancies of <6 months, and satisfactory opinions were obtained about the acceptability and understanding of MCP.

MCP was also applied to cancer survivors (9) in an RCT with a 6-month follow-up, where the MCP condition was compared with two other conditions: (a) a Supportive Group and (b) Treatment as Usual (TAU) with their general practitioner. The results at the 6-month follow-up showed that the MCP treatment improved personal meaning, positive relations, purpose in life, a fighting spirit, hopelessness, goal-orientedness, and psychological wellbeing and adjustment, and it reduced psychological distress and depressive symptoms more than the TAU condition. MCP was more effective in improving goal-orientedness and a fighting spirit compared to the Supportive Group, as well as personal growth and environmental mastery at the 6-month follow-up. In addition, MCP has also been used with people with grief (15) as the Meaning-Centered Grief Psychotherapy (MCGP) for parents who lost a child to cancer. MCGP is an individual and manualized intervention consisting of 16 sessions for people with prolonged grief. In this pilot study, after the intervention, patients showed improvements in grief, depression, meaning in life, positive affect, post-traumatic growth, and quality of life. Finally, MCP has been adapted for caregivers of people with cancer (16), adolescent and young participants with cancer (17), and participants with advanced cancer (4, 18).

As we have seen, MCP has been shown to be effective in improving meaning in life and quality of life and reducing distress in people with cancer. However, it is important to emphasize that all the studies mentioned above on the application of MCP in cancer patients have been carried out in Anglo-Saxon samples and have mainly focused on patients with a diagnosis of cancer in III-IV stages. The construction of meaning, vital goals, responsibility, sources of meaning, and the comprehension and acceptance of these constructs depend on cultural, social, and religious factors, etc. (19). There are studies that indicate that the construction of meaning and growth in the face of adverse situations is different for Anglo-Saxon and Spanish populations. For example, a previous study found that, in the American sample, the presence and search for meaning were moderately and negatively associated, whereas these two factors were uncorrelated in the Spanish population (20). Therefore, it is necessary to adapt and verify the efficacy of MCP in populations that speak languages other than English, such as Spanish and to test the efficacy of MCP in patients with an early stage I–III diagnosis of cancer.

Another psychotherapy that has been found to be effective in participants with cancer is cognitive behavioral therapy (CBT). The adaptation of CBT to participants with cancer is a comprehensive cognitive-behavioral model based on Beck's therapy for depression. The cognitive model of adjustment to cancer states that the patient's assessment, interpretation, and evaluation of cancer is what will determine his/her emotional and behavioral reaction. CBT has been considered a psychological behavioral therapy that, when specifically delivered to cancer patients, focuses on managing emotions, cognitions, problem-solving, relaxation, and assertiveness, and on improving coping with cancer (21). This therapy has been found to be effective in improving anxiety, depression, helplessness, fatalism, anxious preoccupation, and coping (22). CBT has also been found to improve the change in quality-of-life associated with distress due to medical treatments or to adjustment after the disease is treated (23) and lead to greater adaptability to cancer, thus reducing vital anguish (24).

As we can see in the aforementioned RCTs, MCP has been compared to waiting list, TAU with the general practitioner, and active treatments such as supportive therapy. To expand the data supporting the efficacy of MCP for cancer patients, it would be necessary to compare MCP to other active therapies such as CBT. According to the data, no previous studies have compared MCP to active treatments such as CBT for cancer patients, which is the general objective of this study.

The aims of the proposed study are: the first objective is to verify the efficacy of the MCP intervention for Spanish participants with cancer in an RCT comparing it to CBT. The second objective is to analyze the feasibility and acceptance of MCP in Spanish participants with cancer. The third objective is to analyze whether the changes produced in the MIL dimensions (presence, search, comprehension, purpose, and mattering) will predict changes in anxiety, depression, quality of life, etc.

We propose the following hypothesis: (a) After the intervention, all the participants in the two treatment conditions (MCP vs. CBT) will improve on MIL, anxiety, depression, and quality of life; however, the participants in the MCP condition will improve more than those in the CBT condition; (b) After the intervention, both interventions will have good acceptance by the participants, but the MCP condition will have greater acceptance than the CBT condition; (c) The changes produced in the MIL dimensions (presence, search, comprehension, purpose, and mattering) after the intervention will be related to changes in anxiety, depression, and quality of life.

In this article, we present the study protocol.

## Methods and Design

### Study Design

The study design consists of a two-arm RCT with two conditions: MCP and CBT, where participants will be randomized to one of the two groups. Figure 1 contains the flow chart. For this protocol, we will follow the CONSORT statement (Consolidated Standards of Reporting Trials, http://www.consort-statement.org) (25, 26) and the SPIRIT guidelines (Standard Protocol Items: Recommendations for Interventional Trials (27, 28).

**Figure 1 F1:**
[figure not shown]
Flowchart of the study.

### Sample Size

The sample size for this study was generated from effect sizes found in other studies on MCP in participants with cancer, mainly meta-analyses. Dietrich (29) found medium effect sizes for meaning in life (*d* = 0.81), Quality of life (*d* = 0.60), anxiety (*d* = −0.47), and depressive symptoms (*d* = −0.50). These effect sizes are consistent with other studies on MCP in psychological treatments for other mental disorders, such as a meta-analysis by Vos et al. (12) on existential psychotherapies. Based on the results of these studies, we expect an effect size of 0.60 because the study design consists of two experimental groups. To calculate the sample size, we used the G^*^Power 3.1 software (30), taking into account an alpha of 0.05 and a statistical power of 0.80 on a two-tailed *t*-test. We need a sample size of 90 participants (45 participants per condition) to reach an effect size of 0.60 for meaning in life. Finally, we have considered possible sample loss during the treatment program, and based on studies of interventions with MCP, we expect a 30% dropout rate (9). Therefore, taking this outcome into account, our study requires a total sample size of 118 participants (59 participants per experimental condition).

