##### Measures of Primary Outcomes

*Meaning in Life Questionnaire [MLQ*
*(**34**)**]*. The MLQ is a self-reported questionnaire made up of 10 items, and it was developed to assess the two main dimensions of meaning in life: presence and search for meaning in life. The items are rated on a 7-point scale ranging from 1 (absolutely false) to 7 (absolutely true). The factors of Presence and Search were correlated (*r* = −0.19), and internal consistency was good for Presence (0.86) and Search (0.87). One-month test-retest reliability coefficients were 0.70 for Presence and 0.73 for Search.

*The Multidimensional Existential Meaning Scale [MEMS*
*(**35**)**]*. The MEMS assesses the MiL dimensions: Comprehension, purpose, and mattering, with a total of 15 items (e.g., “My life makes sense”; “I have overarching goals that guide me in my life”; “I understand my life”; “I know what my life is”). Likert type responses are given on a 7-point scale (1 = Very strongly disagree; 7 = Very strongly agree). The three MEMS subscales showed adequate internal consistency: Comprehension (ϖ = 91), Purpose (ϖ = 92), and Mattering (ϖ = 86).

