The third objective of this proposed study will be to analyze whether the changes produced in the MIL dimensions (presence, search, comprehension, purpose, and mattering) predict the changes in anxiety, depression, quality of life, etc. In this study, we will use multidimensional measures of meaning to assess change in meaning in life. The MEMS (35) will allow us to evaluate the three dimensions of meaning (comprehension, purpose, and mattering), and the MLQ (36) will allow us to include two other dimensions (presence, search). Evaluating the effectiveness of MCP with multidimensional measures will allow us to find out whether it is effective for all the dimensions of meaning or, on the contrary, produces a change in one dimension (e.g., presence) but not in another (e.g., search). In addition, we will be able to verify which dimension of meaning best predicts the change in the patients' clinical measurements.

Another contribution of this proposed study is the application of MCP through videoconference. To the best of our knowledge, there are no studies on the efficacy of PCM *via* videoconference. This would allow us to take MCP to people who live in places where there are no psychotherapists, so that a greater number of people from very distant places could receive treatment. Some studies have described the advantages of online psychosocial interventions (55), such as compensating for geographical barriers and saving travel time (56). Currently, the number of psycho-oncological pilot studies of online interventions through videoconference in psycho-oncology is increasing. Results have highlighted participant engagement and effectiveness (57, 58). Moreover, a recent randomized control study (59) found similar effectiveness of both face-to-face and online psychotherapy for patients with a diagnosis of cancer with cancer distress. Finally, we must emphasize that we are going to carry out a follow-up at 6 months to confirm whether the results obtained after treatment are maintained, improve, or worsen in both treatment conditions.

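### The stated 80% power and 5% error belong to one test on a single meaning-in-life score, but five dimension scores are primary and no deciding score or success rule is given

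*Protocol article*

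**What the plan says.** The Sample Size section of the protocol article describes a calculation "taking into account an alpha of 0.05 and a statistical power of 0.80 on a two-tailed" t-test, and states "we expect an effect size of 0.60 because the study design consists of two experimental groups". Its result is "We need a sample size of 90 participants (45 participants per condition) to reach an effect size of 0.60 for meaning in life". It names no scale, subscale or time point.

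Measures of Primary Outcomes then lists two instruments. Of the MLQ it says "it was developed to assess the two main dimensions of meaning in life: presence and search for meaning in life". Of the second it says "The MEMS assesses the MiL dimensions: Comprehension, purpose, and mattering, with a total of 15 items". Internal consistency is reported by dimension for both. No total or composite is defined, no dimension is put first, and nothing says whether MCP must be better on one, on a particular one, or on all.

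The Discussion intends a reading by dimension: "Evaluating the effectiveness of MCP with multidimensional measures will allow us to find out whether it is effective for all the dimensions of meaning", and it allows for a change in one dimension but not in another.

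Data Analyses names mixed-effects models, refers in passing to MANOVA results and post hoc comparisons without naming the variables, and leaves the final choice of procedure until the trial is complete.

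**The concern.** The sample size is justified for a quantity that the primary outcomes do not contain. The calculation treats meaning in life as one variable tested once. The outcome section turns it into five variables, and the Discussion expects them possibly to disagree.

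Hypothesis (a) in the Introduction predicts a larger improvement under MCP than under CBT on meaning in life, among other outcomes. It does not say which score would settle this. Followed as written, superiority over CBT could rest on whichever of the five scores reached p<0.05, which does not keep the 5% error that the calculation assumes. A stricter rule would restore the error rate, but the power would then have to be worked out for that rule. The article does neither.

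The five scores are not interchangeable. The article reports a Presence-Search correlation of -0.19 in the MLQ validation, and the Introduction says the two were uncorrelated in a Spanish sample.

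**Working it through.** **Inputs from the article.** Two-sided alpha 0.05, power 0.80, d = 0.60, 45 per arm (Sample Size); two MLQ and three MEMS scores, k = 5 (Measures of Primary Outcomes).

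**Assumed.** The correlations among all five scores are not given, so I take a common correlation of 0, 0.3, 0.5 and 0.7. A variant has Search uncorrelated with the other four. One time point, normal data.

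**1. The plan's own figure.** Two-sample t-test, noncentrality d × √(n/2) = 0.60 × √22.5 = 2.846, 88 degrees of freedom, critical value 1.987. Power is 0.804 at 45 per arm and 0.795 at 44. The stated 45 per arm reproduces, for one score.

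**2. Any of five at unadjusted 0.05, no true difference.** If independent, 1 − 0.95^5 = 0.226. Simulating five correlated t-tests gives about 0.21, 0.19 and 0.15 at correlations 0.3, 0.5 and 0.7. With Search uncorrelated and the other four at 0.7, it is about 17% to 18%.

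**3. All five required, d = 0.60 on each.** If independent, 0.804^5 ≈ 0.34. Simulation gives about 0.44, 0.52 and 0.59 at correlations 0.3, 0.5 and 0.7. Error is held, but power is well below 0.80.

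**4. Bonferroni, 0.05/5 = 0.01 per score.**
- Power for any given score: critical value 2.633, power 0.586. For 0.80 on a given score, 67 per arm are needed.
- Power for at least one win, if all five effects are 0.60: about 0.99, 0.94, 0.89 and 0.83 at correlations 0, 0.3, 0.5 and 0.7. The familywise error is at most 0.05.

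**5. One five-score MANOVA as the decision, all effects 0.60 (Hotelling T², noncentral F).** Power is above 0.99, then 0.91, 0.79 and 0.68 at the same correlations, with error 0.05 for the global question only.

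**6. One named score at one time point.** Power is 0.804 at 0.05, as in step 1.

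The same 90 evaluable participants thus give anything from about 0.34 to about 0.99 power, or an error between 5% and 23%, depending on a rule the article does not state.

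**The case against.** **The multiplicity method may sit in an analysis plan or full protocol that is not shown.** That is fair for the method, and its absence is not the point here. What decides the trial, and what the sample size refers to, belong in the protocol. The article addresses both, and they do not match.

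**The figures are not incompatible.** A reader might infer that 80% power and 5% error cannot both hold with five primary scores. The documents do not support that. Both hold with one named score, with a fixed testing order headed by such a score, or under Bonferroni when one win suffices and all five effects are 0.60. Nor is 0.59 the power of the trial: it is the power for one given score after Bonferroni.

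**The MANOVA may protect the follow-up tests.** A reader might conclude either that it does or that it never could. Used as a gate, it limits the error to 5% when no score truly differs, which is exactly the situation behind the 15% to 23%. Once some scores truly differ, it no longer guarantees the error on the rest. Data Analyses neither names its variables nor makes it a gate, so the article cannot rely on it.

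**Hypothesis (a) does not say that any one score confirms it.** True, but it does not exclude that reading either, and that is the gap.

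**Conclusion.** The point stands in this form: the stated 80% power and 5% two-sided error are correct for one t-test on one score, and are not shown to hold for the five-score primary outcome that the article defines. Under the loosest reading the false-positive rate is about 15% to 23%, three to four and a half times the nominal rate. If all five must be won, power is about 0.34 to 0.59.

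These ranges rest on assumed correlations of 0 to 0.7, a single time point, 45 evaluable per arm, and d = 0.60 on every score where power is quoted. Measures has the primary outcomes collected at five time points, so leaving the time point open as well would add further tests. The matter needs correcting before analysis, because a deciding score chosen after the results are seen would not be credible.

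**What to change.** Before any outcome data are analysed:

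1. In Measures of Primary Outcomes, name one score at one time point as the single primary MCP-CBT comparison, tested at two-sided 0.05. MLQ Presence at post-treatment is one example; the choice is the sponsor's.
2. In Sample Size, tie the calculation to that score and time point. Power stays at 80.4% with 45 evaluable per arm.
3. Make the other four scores, including MLQ Search, key secondary outcomes with a Holm adjustment.
4. If all five are to stay primary, state the success rule (at least one, all, or an ordered sequence) and the adjustment, and restate the power or sample size for that rule.

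The first three steps cost a few sentences and no additional participants or visits. The downside is that a win on another score alone would no longer count as the primary result. Under step 4 the sample size may have to rise: 80% power for each given score under Bonferroni needs 67 evaluable per arm instead of 45.

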However, our study could have some possible limitations. The first limitation we expect to find is the possible dropout rate in both treatment conditions. Treatment efficacy studies have found a dropout rate of 30% (9), which can interfere with the development of the study as well as the type of statistical analysis that we can perform. Another limitation is that the final sample may be composed mainly of older adult women, and because both treatment conditions will be carried out through video conference, this may make it difficult for them to adhere to the treatment conditions. Finally, the sample may be composed mainly of women with breast cancer, which will prevent the generalization of the results to men with other cancer diagnoses.

In sum, coping with cancer implies suffering, pain, hopelessness, low meaning in life, anxiety, and depression in many people (1–3). For this reason, it is necessary to develop effective psychotherapeutic treatments for people with cancer and survivors. Thus, it is necessary to verify the effectiveness of MCP by comparing it to well-established treatments. This will allow us to confirm whether MCP can become another well-established treatment for people with cancer.

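### The 30% dropout allowance multiplies 45 per arm by 1.3 instead of dividing by 0.7, so on the planning t-test 118 participants give about 77% power at that dropout rate, not 80%

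*Protocol article*

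**What the plan says.** The calculation is in the Sample Size section of the protocol article, under Methods and Design. The test is specified by "taking into account an alpha of 0.05 and a statistical power of 0.80 on a two-tailed" t-test, and the effect by "we expect an effect size of 0.60 because the study design consists of two experimental groups". From these the article obtains its evaluable number: "We need a sample size of 90 participants (45 participants per condition) to reach an effect size of 0.60 for meaning in life". It then turns to losses during the treatment programme and says "we expect a 30% dropout rate (9"), where 9 is a literature citation. The final number follows directly: "Therefore, taking this outcome into account, our study requires a total sample size of 118 participants (59 participants per experimental condition").

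The limitations paragraph of the Discussion repeats the rate: "Treatment efficacy studies have found a dropout rate of 30% (9"). The article gives no other dropout rate and no other basis for 118.

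**The concern.** An allowance for dropout should ensure that the required number is still present after the expected loss. That means dividing the evaluable number by the proportion retained. Adding 30% of the evaluable number gives too few, because the 30% loss then applies to the larger, inflated number.

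The article gives three figures: 90 needed, 30% lost, 118 required. They cannot all be correct. A reader would take from them that the trial keeps 80% power on the planning test if 30% drop out, and on the plan's own inputs it does not. Dropout is also the first limitation the Discussion names, so this allowance should be right. If it is not corrected, the sentence is likely to be carried into the results report.

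**Working it through.** **Inputs, all from the Sample Size section:** two-sided alpha 0.05; power 0.80; standardised difference d = 0.60; equal allocation; 45 evaluable per arm (90 in total); dropout 30%; stated requirement 59 per arm (118 in total).

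**Step 1. Reproduce the base.** For a two-sample t-test (noncentral t) with n per arm, the noncentrality is d x sqrt(n/2).
- Solving for 80% power gives n = 44.59, so 45 per arm.
- Power is 0.795 at n = 44 and 0.804 at n = 45.
- The stated 90 (45 per arm) is therefore right.

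**Step 2. Reproduce the stated total.**
- Multiplying: 45 x (1 + 0.30) = 58.5, rounded up to 59 per arm; 2 x 59 = 118. This matches exactly.
- Dividing: 45 / (1 - 0.30) = 64.3, rounded up to 65 per arm; 2 x 65 = 130.
- Worked on the total without requiring equal arms: 90 / 0.70 = 128.6, so 129.

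Only multiplication gives 118. The shortfall is 12 participants with equal arms (130 - 118), or 11 on the total (129 - 118).

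**Step 3. What 118 delivers at 30% dropout**, if dropouts give no post-treatment outcome.
- Remaining: 118 x 0.70 = 82.6, or 41.3 per arm; 90 - 82.6 = 7.4 below the plan's own requirement.
- Power at d = 0.60:

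| Evaluable per arm | Power |
|---|---|
| 41 | 0.765 |
| 41.3 | 0.769 |
| 42 | 0.776 |
| 45 (plan's target) | 0.804 |
| 45.5 (65 x 0.70) | 0.808 |

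**Step 4. The dropout that 118 can absorb.** 1 - 90/118 = 0.237, so 118 keeps 90 evaluable up to 23.7% dropout.

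**Step 5. Sensitivity to baseline adjustment.** If the between-arm contrast is adjusted for the baseline score, and r is the baseline-to-outcome correlation, the effective difference is approximately 0.60 / sqrt(1 - r^2). The article does not give this correlation for these participants, so r is an assumption and is shown over a range. At 41 per arm, ignoring clustering by therapy group:

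| Assumed r | Effective d | Power |
|---|---|---|
| 0 | 0.600 | 0.765 |
| 0.2 | 0.612 | 0.782 |
| 0.3 | 0.629 | 0.803 |
| 0.4 | 0.655 | 0.834 |
| 0.5 | 0.693 | 0.873 |

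The break-even for 80% is r of about 0.29.

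**The case against.** The strongest reply is that the trial will not be analysed by the planning t-test. The Data Analyses section plans intention-to-treat mixed-effects models with full-information maximum likelihood, and the Measures section lists five assessments. Someone who leaves therapy may still complete questionnaires, and someone with partial data still enters the model. The 82.6 in Step 3 assumes that every dropout gives no post-treatment outcome, which the article does not say. If all 118 were assessed, t-test power would be 0.898.

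This stands as a limit on the finding. A reader might infer that the trial as analysed will fall below 80% power, and the document does not support that. Power under the mixed model depends on how much outcome data dropouts give and on correlations that the article does not state. The reply does not rescue the sentence, however. The Sample Size section sizes the trial on a t-test and makes an explicit allowance for lost participants, and on that basis 118 is not what a 30% loss requires. A participant who leaves before any post-treatment assessment gives only a baseline score, which adds little about the treatment difference.

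The opposite inference, that baseline adjustment simply makes up the loss, is also too strong. It does so only if the correlation is about 0.29 or more. The one-month retest coefficients quoted for the meaning questionnaire (0.70 and 0.73) do not settle this. They are not correlations across a two-month intervention, and participants here are selected for scores below 105 on the Purpose in Life test, which could lower the correlation. Both therapies are given in groups, and the figures above ignore that.

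It can also be said that the shortfall is small beside the uncertainty in d = 0.60, which was chosen from published effects of 0.47 to 0.81 in absolute size. That is fair, and it bears on severity. It does not make the arithmetic right.

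**Conclusion.** The stated total is wrong for the plan's own inputs. The allowance was multiplied on instead of divided out, which gives 118 where 130 (65 per arm) is needed to keep 45 evaluable per arm after a 30% loss. On the planning t-test, with d = 0.60, two-sided alpha 0.05, no post-treatment outcome from dropouts and no clustering by therapy group, power at 30% dropout is about 77%, or about 3 points below the stated 80%.

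The point goes no further than that. The base of 90 is correct, no planned analysis or estimate is invalidated, and it is not shown that the mixed-model analysis would be underpowered. This is a should-fix correction of a stated figure.

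**What to change.** Correct the last sentence of the Sample Size section in one of two ways:

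- **Keep the number and restate what it gives:** *118 randomised (59 per arm) gives 80% power if dropout is at most about 24%, and about 77% at 30% dropout.*
- **Keep the assumptions and restate the number:** 130 randomised (65 per arm).

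The first costs one sentence and a slightly less favourable figure, with no new participants. The second costs 12 more participants.

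Optionally, if 118 is kept and the between-arm contrast is to be adjusted for the baseline score, which is already collected, power can be stated on that basis. The assumed correlation should then be given with a range such as the one in Step 5 (about 78% at 0.2, 80% at 0.3, 83% at 0.4 and 87% at 0.5), with a note that clustering by therapy group is ignored. The arithmetic correction does not depend on this.
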